#### Secondary outcomes

Using the same statistical procedure described above, we will assess behavioral intent to seek health information with E-E media. To establish participant engagement with the CoVideo, we will use a logistic regression model to estimate the proportion of participants in the APC and control arms that chose to watch the CoVideo, adjusting for the knowledge scores and demographic factors. We will use either an OLS model or Cox proportional hazards model to model the time to when a person clicks “Finish Video” (right censoring) or when the CoVideo ends naturally (left censoring). We will use R statistical software to undertake the analysis.

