#### Secondary outcome measure

We will assess participant’s behavioral intent to seek health information from online, animated videos. Because of social desirability bias, we will again use a list experiment with the same procedures described in Table 2. The list experiment will read: *This week, I will seek health information from: Television news channels; Social media celebrities; Religious leaders on the Internet; Public health agency websites; Conversations with family and friends; *Animated videos made by health experts*. (The sensitive item is indicated by an asterisk (*).)

We aim to measure participant engagement with the CoVideo. At the end of the survey, we will offer the APC and no-video arms the choice to watch the CoVideo or end the survey. The Gorilla platform will record this response. If the “Watch Video” button is clicked, Gorilla will record the time (in milliseconds) from the video start until the participant clicks the “Finish” button (or until the video ends at 2.30 min, whichever comes first). This data will be used to assess objective 3.

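### The censoring labels for the Cox option in the viewing-time analysis are wrong: an exactly observed Finish click is called right-censored, and reaching the video's end is called left-censored

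*Protocol article*

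**What the plan says.** The measurement is defined in the Protocol article under Secondary outcome measure. Its purpose is engagement ("We aim to measure participant engagement with the CoVideo"), and it applies to those who accept an offer at the end of the survey: "we will offer the APC and no-video arms the choice to watch the CoVideo or end the survey". The clock for those who watch is described in these words: "Gorilla will record the time (in milliseconds) from the video start until the participant clicks the". The button meant is the one that ends viewing early. A cap is then set on the same clock: "or until the video ends at 2.30 min, whichever comes first".

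The analysis is given in the statistical methods under Secondary outcomes: "We will use either an OLS model or Cox proportional hazards model to model the time to when a person clicks". That sentence names two ways in which viewing ends, a click on the button and the video running out. The bracketed labels attached to these two outcomes read "right censoring) or when the CoVideo ends naturally (left censoring". The same section plans a logistic regression for the choice to watch at all.

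**The concern.** Viewing can end in only two recorded ways, by a click or by the video running out, and the plan calls both of them censoring. A Cox model needs at least one outcome to count as the event. Calling the natural end left-censored also reverses what is known about those viewers: it says that their stopping time lay at or before the end, when in fact they had not stopped by then.

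At stake is whether the Cox option can be run as written. If it cannot, the event definition has to be settled later, possibly with the data in view; Trial status already reports 14,800 completed surveys.

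**Working it through.** The protocol gives no event count, sample size or power for this analysis, so there is no figure to reproduce. The check applies the definitions of censoring to the recorded variable.

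**Recorded variable.** Let T be the time at which a viewer would click Finish and L the video length. The outcome-measure section gives recorded time Y = min(T, L).

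| How viewing ends | What is known about T | Correct status | Protocol label |
|---|---|---|---|
| Click before the end | T = Y exactly | Event | Right censoring |
| Video runs to its end | T ≥ L | Right-censored at L | Left censoring |

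Left censoring would need T ≤ Y with T itself unobserved. That cannot arise here, because timing starts with the video and every click is time-stamped.

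**Could another reading rescue the labels?**

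1. *Both labels as written.* There are 0 events. The Cox partial likelihood is an empty product and carries no information on any coefficient.
2. *Labels swapped.* The natural end becomes right-censored, which is correct, but the click becomes left-censored. There is still no event.
3. *Completion is the event and a click right-censors it.* The natural end would then be an exact event time, so left censoring is still the wrong label. All d events fall at L, and only those same d completers are at risk there. For a binary covariate with d₁ completers in one group and d₀ in the other, the Breslow log partial likelihood is d₁β − d·log(d₀ + d₁e^β). Setting its derivative to zero gives d·e^β = d₀ + d₁e^β. Since d = d₀ + d₁, this means e^β = 1. The hazard ratio is 1 whatever the data.

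**Illustration.** Assumptions, none from the protocol: 4,000 watchers; exponential click times with a reference-group median of 60, 150 or 400 s; a binary covariate with true hazard ratio 0.8; L of 150 s or 138 s, the two readings of 2.30 min. One simulated data set per row; SE is for the log hazard ratio.

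| L (s) | Median (s) | Clicks before end | HR (SE), click = event | HR, completion = event | Mean difference, recorded time (s) | Mean difference, uncapped (s) |
|---|---|---|---|---|---|---|
| 150 | 60 | 3,135 | 0.850 (0.036) | 1.000 | 7.5 | 19.8 |
| 150 | 150 | 1,809 | 0.762 (0.047) | 1.000 | 8.7 | 60.2 |
| 150 | 400 | 874 | 0.801 (0.068) | 1.000 | 4.6 | 147.8 |
| 138 | 60 | 3,034 | 0.770 (0.036) | 1.000 | 11.5 | 22.9 |
| 138 | 150 | 1,724 | 0.847 (0.048) | 1.000 | 4.1 | 46.7 |
| 138 | 400 | 772 | 0.863 (0.072) | 1.000 | 3.0 | 144.3 |

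With both outcomes censored, the fit stopped with an error in all six settings. With the click as the event, it ran in all six and gave estimates scattered around 0.8.

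**The OLS option.** OLS on recorded time needs no event indicator, so the labels do not touch it. It estimates the mean of min(T, L), not the mean of T. An example by hand, with assumed exponential means of 200 s and 150 s and L = 150 s:

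- Share reaching the end: exp(−150/200) = 0.47 and exp(−150/150) = 0.37.
- Restricted means: 200 × (1 − 0.472) = 105.5 s and 150 × (1 − 0.368) = 94.8 s.
- Difference: 10.7 s restricted, against 200 − 150 = 50 s unrestricted.

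Both are legitimate quantities, but they are different ones.

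**The case against.** The best defence is that the intent is recoverable. The statistical section names the click as what is being timed, and the outcome-measure section describes the cap correctly. An analyst reading the two together could identify the event and the censoring point and ignore the bracketed terms. The raw times are kept in milliseconds, so event status can be derived at any stage. Both faulty codings would also show themselves, one as a failed fit and the other as a hazard ratio of exactly 1, so neither is likely to reach a report unnoticed. All of this stands, and it limits the harm. It does not make the stated rule correct, and nothing else in the article corrects it.

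A reader might infer more than the text supports:

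- *That the viewing-time analysis as a whole cannot be run, or that every viewing-time record is compromised.* This would follow only if Cox is chosen and the labels are coded literally. The protocol also allows OLS.
- *That objective 3 is undermined.* That objective is voluntary interest in watching, and its most direct analysis is the logistic model for the choice to watch, which does not use these labels.
- *That the plan would yield a plausible but misleading hazard ratio.* The working shows a degenerate result instead.
- *That Cox must replace OLS.* Either can be defended, and the final choice may sit in an analysis plan that is not shown.

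**Conclusion.** The labels are wrong on every reading, and this is a misstated rule, not a detail left to another document. That conclusion rests only on the protocol's own definition of the recorded time. The illustrative hazard ratios and mean differences rest on assumed click-time distributions and say nothing about this trial's likely results.

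The point is a small one. It bears on one secondary engagement measure, and only under the Cox option. The participants concerned are those in arms 2 and 3 who choose to watch: at most 17,010 × 2/3 = 11,340, with the share who accept not stated. The primary outcomes, the list experiments and the logistic analysis are unaffected. It should be corrected before the viewing-time analysis is run, but it does not threaten the trial's main conclusions.

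**What to change.** Replace the bracketed labels with a statement that the event is a Finish click before the video ends, and that viewers who reach the end are right-censored at the video's full length. Give that length in seconds, since 2.30 min can be read as 138 s or 150 s.

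If OLS on recorded time is used instead of, or beside, the Cox model, describe its estimate as mean viewing time restricted to the video length.

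The cost is a sentence or two in the protocol or analysis plan. No new data are needed, because the recorded times already determine event status.

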#### Interim analyses

No interim analyses are planned.

#### Methods for additional analyses (e.g., subgroup analyses)

We will conduct both country-specific and cross-country pooled analyses, provided sufficient sample sizes can be recruited from each country.

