## Methods: participants, interventions, and outcomes

### Study setting

This will be an online study setting. We will use the online recruitment platform Prolific Academic (ProA: https://www.prolific.co) to enroll participants from the USA, the UK, Germany, Spain, Mexico, and France. We will host and deploy our study on an online platform called Gorilla™ (www.gorilla.sc) (Fig. 2).

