### Sample size

We calculated the sample size needed for pairwise comparisons between three groups using a one-way analysis of variance (ANOVA). The formula to calculate the sample size is [18]:

$$ {n}_A=\left({\sigma}_A^2+{\sigma}_B^2/\kappa \right){\left(\frac{Z_{1-\frac{\alpha }{\tau }}+{Z}_{1-\beta }}{\mu_A-{\mu}_B}\right)}^2 $$where *κ* = 1, which is the matching ratio; *μ*_*A*_ and *μ*_*B*_ are the group A and B means; *σ*_*A*_ and *σ*_*B*_ are the group A and B standard deviations; *α* = 0.05 is the type-I error; *β* = 0.20 is the type-II error; *Z* is the quantile function; and *τ* = 2 is the number of comparisons to be made. To detect a small difference of 0.1 between the knowledge scores of two trial arms, we assumed a mean of *μ*_*A*_ = 14.0 and *μ*_*B*_ = 14.1 and *σ*_*A*_ = 1.5 and *σ*_*B*_ = 1.5. We select *μ* on the expectation that participants will get 14 out of 18 knowledge items correct. This gives a sample size of *n*_*A*_ = *n*_*B*_ = *n*_*C*_ = 3,532, so *N* = 10,596. If we change our assumption about *σ* and increase it to *σ* = 1.8, then the required sample size becomes *n*_*A*_ = *n*_*B*_ = *n*_*C*_ = 5,087 and *N* = 15,261. For the list experiment, we selected a sample size to detect a small difference of 0.05 between the control list group and the treatment list group. Because we framed the list questions to avoid floor and ceiling effects, we expect, on average, that the control group will agree with 2 out of the 5 items and the treatment group 2.05 of the 6 items. We selected *σ*_*A*_ = 0.7 and *σ*_*B*_ = 0.8, allowing the second *σ* to be larger because of the additional sensitive item. This calculation gives a sample size of *n*_*A*_ = *n*_*B*_ = *n*_*C*_ = 3,548 and *N*= 10,644. If we change our assumption about *σ* and increase it to *σ*_*A*_ = 0.9 and *σ*_*B*_ = 1.0, then we have *n*_*A*_ = *n*_*B*_ = *n*_*C*_ = 4,553 and *N* = 13,659. For this study, we will recruit 17,010 participants, more than the 15,261 calculated sample size, to ensure our study is sufficiently powered.

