### Recruitment

To be recruited, a person must open an account on ProA and provide his or her personal information. Participants must agree to ProA’s data privacy terms and conditions. ProA will assign each participant a unique, anonymized ID. The study investigators will also open an account on ProA. We will instruct the ProA platform on how many participants need to be recruited. ProA will filter out all participants who do not meet the eligibility criteria. Participant recruitment will happen on a “first come, first served” basis until the recruitment number (sample size) is reached. We will compensate the participants an equivalent of £1 for the expected 10-min completion time.

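### Country-specific analyses depend on an unquantified sample-size condition; one arm-by-country model reporting all six countries would be safer

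*Protocol article*

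**What the plan says.** Study setting in the protocol article says the platform will be used "to enroll participants from the USA, the UK, Germany, Spain, Mexico, and France". Recruitment describes how places are filled: "Participant recruitment will happen on a “first come, first served” basis until the recruitment number (sample size) is reached". No quota, cap or minimum for any country is stated.

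The Sample size section works out per-arm numbers for comparisons across the whole trial and ends: "For this study, we will recruit 17,010 participants, more than the 15,261 calculated sample size, to ensure our study is sufficiently powered". It contains no calculation for a single country.

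The only sentence on country analyses, under Methods for additional analyses, is "We will conduct both country-specific and cross-country pooled analyses, provided sufficient sample sizes can be recruited from each country". The section does not say what number is sufficient, does not refer back to Sample size, and does not mention a test of whether the effect differs between countries.

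**The concern.** The condition "provided sufficient sample sizes can be recruited from each country" can be judged only when recruitment has ended and the country counts are visible. With no threshold fixed, the decision on which countries get their own analysis falls at that point, and it could be influenced by more than the counts.

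There is also a problem of interpretation. Suppose the video has the same effect everywhere. Separate tests in strata of different size will then tend to be significant in the large ones and not in the small ones. A reader could take this pattern as evidence that the video works in some countries and not in others, when it shows only who signed up first. What answers the question of country differences is a direct test of heterogeneity, and the stated approach has none.

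**Working it through.** **Inputs.** From Sample size: difference 0.1 on the knowledge score; SD 1.5, or 1.8 in the more cautious case; α = 0.05 divided by τ = 2, which acts as a two-sided 5% test (z = 1.960); power 80% (z = 0.842); 17,010 to be recruited. From Trial design: three arms at 1:1:1. From Study setting: six countries.

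**The plan's own figures.** n per arm = (σ_A² + σ_B²) × ((1.960 + 0.842)/0.1)².
- SD 1.5: 4.50 × 784.9 = 3,532 per arm; × 3 = 10,596. This agrees with the article.
- SD 1.8: 6.48 × 784.9 = 5,086.1, rounded up to 5,087; × 3 = 15,261. This agrees.

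Both totals describe one set of three arms pooled over countries.

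**One country at an equal split (assumption).** The documents give no country counts, so equal shares serve as a neutral reference: 17,010/6 = 2,835 per country, and 2,835/3 = 945 per arm.
- Standard error of a difference = SD × √(2/945): 0.069 at SD 1.5; 0.083 at SD 1.8.
- Power for 0.1 = Φ(0.1/SE − 1.960): Φ(−0.511) = 30%; Φ(−0.752) = 23%.
- Difference detectable with 80% power = 2.802 × SE: 0.19; 0.23.

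If the true effect were 0.1 in every country and each were tested separately, the expected number of non-significant countries would be 6 × (1 − 0.305) = 4.2 at SD 1.5, or 6 × (1 − 0.226) = 4.6 at SD 1.8.

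**An uneven split (illustration only).** Let one country supply 10,596 and the other five share the remaining 17,010 − 10,596 = 6,414 equally. Each of the five then has about 1,283 participants, or 428 per arm. At SD 1.5 with a common effect of 0.1, the large country has 80% power and each of the others about 16%. The pattern of significance would follow the country mix although the effect is identical.

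**The case against.** The strongest reply is that the 0.1-point target belongs to the pooled trial. The article never says that each country must detect 0.1 with 80% power, and the country sentence stands under additional analyses. Subgroups with less power than the main comparison are normal, and no stated objective concerns country differences. This stands, and it rules out a stronger reading.

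A reader might infer that at most one country can ever qualify, because neither 10,596 nor 15,261 fits twice into 17,010. The arithmetic is right, but it carries the pooled target over to an analysis that the article does not tie to it. With a target of 0.2 points at SD 1.5, a country would need 3 × 883 = 2,649, and an equal split supplies 2,835. The documents do not set that target either, so they do not show the condition to be unattainable.

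It can also be said that a minimum stratum size is a matter for the statistical analysis plan, which is not shown. That holds for the missing number on its own. It does not remove the objection to the method the article does state, namely separate country analyses conditional on the size reached.

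Finally, the article does not say that countries will be compared on their p-values. The misreading is a risk that this method leaves open; it is not an announced procedure.

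**Conclusion.** The point holds as a weakness of an additional analysis. The article makes country-specific analyses conditional on a size that is not quantified and can be judged only after recruitment, while order of arrival determines the country mix. The power of 30% or 23%, and the detectable difference of 0.19 or 0.23, rest on two assumptions: equal country shares, and the pooled target of 0.1 applied to each country. Any country with fewer than 945 per arm would have less power, and any with more would have more. No country limit is stated, though unreported limits on the platform cannot be excluded.

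The primary pooled comparison is not affected. Nor do the documents support saying that the country question would be answered wrongly: an imprecise country estimate from a randomized comparison is still a valid estimate, and running no country analysis gives no answer at all.

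A reader might also infer that country quotas are the remedy. They are not. The low power above already assumes the evenest possible split. Trial status reports 14,800 completed surveys, which leaves only 17,010 − 14,800 = 2,210 places.

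**What to change.** In Methods for additional analyses, replace the conditional country-specific analyses with the following:

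- Fit the pooled OLS model with arm, country and their interaction, and test the interaction; with three arms and six countries it has 2 × 5 = 10 degrees of freedom. For the list outcomes the corresponding term is arm by list by country.
- Report the effects in all six countries with confidence intervals, whatever the number recruited in each.
- Label these results exploratory and make no claim of significance for a single country.

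This removes the choice of countries after the counts are known and puts the question of heterogeneity to a direct test. It needs no new data and no change to recruitment. Since Interim analyses states that none are planned, the wording can be settled before the outcome analysis.

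The cost is one extra model per outcome and some imprecise estimates on display. At an equal split, the 95% interval for a knowledge difference would have a half-width of 1.96 × 0.069 = 0.14 at SD 1.5, or 1.96 × 0.083 = 0.16 at SD 1.8, and wider in smaller countries. The interaction test will also have limited power against small differences between countries, so a non-significant result should not be presented as proof of a common effect.

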#### Methods in analysis to handle protocol non-adherence and any statistical methods to handle missing data

Participants will have a 30-s time limit to answer each knowledge item. This limit is to prevent participants from searching for answers on the Internet. If the participant times out, they will receive a missing value of 9. This missing value will be recoded as an incorrect answer to the knowledge item, since the participant could not correctly answer the question in the allotted time.

#### Plans to give access to the full protocol, participant level-data, and statistical code

This document is the full protocol. Anyone interested in other data or documentation should contact the corresponding author.

### Oversight and monitoring

#### Composition of the coordinating center and trial steering committee

The trial will be overseen by a trial steering committee (TSC). The TSC will have an independent chairperson and members but also includes the trial collaborators. Two TSC meetings are planned.

#### Adverse event reporting and harms

It is unlikely there will be adverse events given the online format of the trial. The auditing of trial conduct will be addressed in the two TSC meetings.

#### Dissemination plans

We will disseminate the study findings through journal publications and conference presentations.

## Discussion

There is a critical need for public health actors to disseminate scientific information about the prevention of COVID-19, especially in the absence of a vaccine. To this end, we have produced a short, animated E-E video to improve knowledge of, and behavioral intent, toward preventive COVID-19 behaviors. In this study, we propose to evaluate the effectiveness of our E-E video using three innovative approaches.

First, we will use state-of-the-art online technology to implement our multi-site randomized controlled trial. The ProA platform will enable us to rapidly recruit a large and diverse number of participants who speak different languages and live in different countries in Europe, North America, and Latin America. Second, we will implement the study on the Gorilla platform, which is designed to host and facilitate experimental trials in behavioral research. The Gorilla platform will enable us to randomize at two different levels: (1) participants will be randomized to the E-E intervention, the APC, or the control arm; (2) within each arm, participants will then be randomized to receive a control list or treatment list. Further, the list experiments will also be randomly ordered to avoid order effects. All randomization will be performed automatically by the Gorilla randomization algorithm, which demonstrates the platform’s potential to implement innovative trial designs and concepts.

Third, we will use a list experiment as the primary outcome of this study. Given the unprecedented nature of the COVID-19 outbreak, and the media attention it has received, we assume that participants will already be primed to give socially acceptable responses to questions about COVID-19. In public, individuals will say they will adhere to social distancing recommendations. But in private, they may attend secret “corona parties” [19]. The list experiment gets around the problem of eliciting untruthful answers to socially desirable questions. Further, we have designed the trial in a way, making full use of the Gorilla features, to measure the magnitude of social desirability bias toward the COVID-19 questions.

We expect that our study will make important contributions to the E-E literature. Importantly, lessons learned can help us to improve the design of E-E videos to disseminate public health information for future pandemics. And we may hopefully demonstrate that our E-E video, which has been viewed more than a million times on social media thus far, will have contributed to current public health efforts to keep people safe and reduce the spread of COVID-19. Our results will also guide future E-E strategies to support the long-term COVID-19 response, as countries are easing first-wave lockdown or reimplementing second-wave lockdowns.

